# Pragmatic, open-label, single-center, randomized, phase II clinical trial to evaluate the efficacy and safety of methylprednisolone pulses and tacrolimus in patients with severe pneumonia secondary to COVID-19: The TACROVID trial protocol

**DOI:** 10.1016/j.conctc.2021.100716

**Published:** 2021-01-19

**Keywords:** COVID-19, SARS-CoV-2, Methylprednisolone, Tacrolimus, Inflammation, Lung injury

## Abstract

**Introduction:**

Some COVID-19 patients evolve to severe lung injury and systemic hyperinflammatory syndrome triggered by both the coronavirus infection and the subsequent host-immune response. Accordingly, the use of immunomodulatory agents has been suggested but still remains controversial. Our working hypothesis is that methylprednisolone pulses and tacrolimus may be an effective and safety drug combination for treating severe COVID-19 patients.

**Methods:**

and analysis: TACROVID is a randomized, open-label, single-center, phase II trial to evaluate the efficacy and safety of methylprednisolone pulses and tacrolimus plus standard of care (SoC) versus SoC alone, in patients at advanced stage of COVID-19 disease with lung injury and systemic hyperinflammatory response. Patients are randomly assigned (1:1) to one of two arms (42 patients in each group). The primary aim is to assess the time to clinical stability after initiating randomization. Clinical stability is defined as body temperature ≤37.5 °C, and PaO2/FiO2 > 400 and/or SatO2/FiO2 > 300, and respiratory rate ≤24 rpm; for 48 consecutive hours.

**Discussion:**

Methylprednisolone and tacrolimus might be beneficial to treat those COVID-19 patients progressing into severe pulmonary failure and systemic hyperinflammatory syndrome. The rationale for its use is the fast effect of methylprednisolone pulses and the ability of tacrolimus to inhibit both the CoV-2 replication and the secondary cytokine storm. Interestingly, both drugs are low-cost and can be manufactured on a large scale; thus, if effective and safe, a large number of patients could be treated in developed and developing countries.

**Trial registration number:**

NCT04341038 / EudraCT: 2020-001445-39

## Abbreviations

CoV =CoronavirusSARS-CoV =Severe Acute Respiratory Syndrome CoronavirusMERS-CoV =Middle East Respiratory Syndrome CoronavirusSARS-CoV-2 =Severe Acute Respiratory Syndrome Coronavirus 2COVID-19 =Coronavirus disease 2019SoC =Standard of CarePaO2 =arterial oxygen partial pressureSatO2 =Oxygen saturationFiO2 =fractional inspired oxygenPIC =pro-inflammatory cytokinesHLH =hemophagocytic lymphohistiocytosisCADM =clinically amyopathic dermatomyositisMDA-5 =anti-melanoma differentiation-associated gene 5RT-PCR =Reverse transcription polymerase chain reactionLDH =lactate dehydrogenaseCRP =c-reactive proteinALT =alanine aminotransferaseICF =informed consent formECMO =extracorporeal membrane oxygenationGFR =Glomerular filtration rateBMI =body mass indexPSI =Pneumonia Severity IndexSOFA score =Sequential Organ Failure Assessment Score6MWT =6-min walk testeCRF =electronic case report formARDS =acute respiratory disease syndromeJAK =Janus KinaseIL =interleukinBUH =Bellvitge University Hospital

## Background

1

In December 2019, an emerging disease (COVID-19), caused by a newly identified human coronavirus (SARS-CoV-2), was first recognized in Wuhan, China and spread worldwide [1,2]. The WHO declared the COVID-19 epidemic to be a pandemic on March 12, 2020 [3].

Unfortunately, there are still no proven effective and safe therapies for treating the COVID-19 illness other than supportive care. Despite the lack of evidence, the urgency of care leads to a large number of severe patients receiving off-label and compassionate use therapies, based on their in vitro antiviral or immunomodulatory properties. Among suggested treatments, the repositioning of older drugs may be a plausible strategy given that their proven safety profile [4,5]. Furthermore, there are several ongoing randomized controlled trials (RCTs) assessing different drug regimens for treating patients with COVID-19 [6].

Of great concern, some COVID-19 patients evolve to fatal lung injury and multi-organ failure due to the serious inflammatory process triggered by the viral infection [[7], [8], [9], [10], [11], [12]]. While the use of some immunosuppressive drugs has been reported to be potentially harmful, other such drugs, paradoxically, have been justified in treating the excessive inflammation triggered by the viral infection [13]. Unfortunately, studies performed following pragmatic randomized controlled trials (pRCT) are still very limited to date and current international recommendations have not taken a position either in favor of or against the use of immunomodulatory therapy in such patients.

Our working hypothesis is that methylprednisolone pulses and tacrolimus might be an effective and safe drug combination strategy for severe COVID-19 patients. Accordingly, given the rapid spread of COVID-19 and the current health emergency worldwide, we performed a proof-of-concept study in a randomized, open-label, single-center, clinical trial to evaluate the efficacy and safety of methylprednisolone and tacrolimus plus standard of care (SoC), versus SoC alone, in severe COVID-19 patients with lung injury and systemic hyperinflammatory syndrome.

The rationale for the present pRCT is based on the fact that glucocorticoids such as methylprednisolone are a mainstay in the treatment of several immune-mediated disorders, with multiple mechanisms of action involving both the humoral and cell-mediated arms of immunity. As for tacrolimus, the rationale for its use is based on its specific mechanism of action leading to an impaired lymphocyte function and a decrease in pro-inflammatory cytokines (PIC) [14]. Interestingly, severe COVID-19 disease presents a fairly similar clinical and cytokine profile to other diseases such as secondary hemophagocytic lymphohistiocytosis (sHLH) [15] or clinically amyopathic dermatomyositis (CADM) associated with anti-melanoma differentiation-associated gene 5 (MDA-5), where calcineurin inhibitors such as tacrolimus or cyclosporine play a central role in its treatment [16]. Furthermore, some human coronavirus (CoV) replication depends on active immunophilin pathways, which can be inhibited by tacrolimus, at low, non-cytotoxic concentrations in cell culture [17]. In this regard, anecdotal case series suggest that tacrolimus may exert a protective effect in solid organ transplanted patients affected by MERS-CoV [13]. Thus, tacrolimus has an immunosuppressive effect but would also block viral replication and may have beneficial impacts on severe COVID-19 lung injury.

## METHODS: (no word limit)

2

### Study design

2.1

TACROVID is a pragmatical, randomized (1:1), open-label, single-center, phase II clinical trial to evaluate the efficacy and safety of methylprednisolone pulses and tacrolimus plus SoC, versus SoC alone, in severe COVID-19 patients with lung injury and systemic hyperinflammatory syndrome.

### Population

2.2

Patients are being prospectively recruited and included in the study for subsequent randomization, if they meet all the inclusion criteria and there is no reason for exclusion.

#### Inclusion criteria

2.2.1

1)COVID-19 infection confirmed by nasopharyngeal RT-PCR,2)New pulmonary infiltrates (either by chest X-ray or computerized axial tomography),3)Respiratory failure (PaO2/FiO2 <300 or satO2/FiO2 <220),4)High analytical inflammatory parameters (CRP >100 mg/L, and/or D-Dimer >1000 μg/L and/or Ferritin >1000 μg/L).

#### Exclusion criteria

2.2.2

1)Critically ill patients with life expectancy ≤24h,2)Glomerular filtration ≤30 mL/min/1.73 m^2^,3)Leukopenia ≤4000 cells/μL or other conditions that cause immunosuppression,4)Concomitant potentially serious infections,5)Contraindication for the use of corticosteroids or tacrolimus according to the Summary of Product Characteristics,6)Known hypersensitivity to any of the study drugs, their metabolites, or formulation excipient,7)Previous participation in a RCT in the last 3 months.

All patients (or a legal representative) have to provide informed consent (ICF) prior to initiation of the study procedures.

### Setting

2.3

The TACROVID trial is being conducted at Bellvitge University Hospital (BUH), a 750-bed tertiary care public hospital in Barcelona (Catalonia, Spain). BUH is the reference hospital for high complexity patients from the Southern Area of Catalonia, a region of approximately 2 million inhabitants.

### Randomization

2.4

On day 0, patients are centrally and randomly assigned using the RedCap computer platform that allows data collection and patient randomization. Patients are not stratified by baseline variables. Participants are randomized in a 1:1 ratio into one of two study groups: methylprednisolone pulses, tacrolimus and SoC, or SoC alone.

### Treatment

2.5

Patients are being randomly assigned to one of the following arms:1. Experimental: methylprednisolone pulses of 120 mg/day are administered on 3 consecutive days (if not previously administered) and immediate release tacrolimus is administered twice daily until clinical stability is achieved. Tacrolimus dosing is individualized through therapeutic drug monitoring (TDM) to achieve blood trough levels of 8–10 ng/mL. In addition, patients in the experimental arm can receive standard of care (SoC) for their management in accordance with treating physicians.2. Control (SoC): SoC includes measures of supplemental oxygen and respiratory support, fluid therapy, antipyretic treatment, postural measures, low molecular weight heparins, and may also include other treatments, whether antiviral or immunosuppressive drugs, or those necessary at the discretion of the treating physician, except for cyclosporine and/or tacrolimus.

The experimental drugs start immediately after having been randomly assigned to this group. The experimental treatment is discontinued after “*clinical stability*”, which is achieved after fulfilling all of the following criteria for 48 consecutive hours: body temperature ≤37.5 °C; PaO2/FiO2 > 400 and/or SatO2/FiO2 > 300; and respiratory rate ≤24 rpm.

Experimental treatment is also discontinued if the included patient has a severe or potentially severe infection, required invasive mechanical ventilation, extracorporeal membrane oxygenation (ECMO), or has any serious medication-related adverse event (of special interest refractory HTA, decrease of more than 50% of the GFR compared to the baseline, or ventricular tachycardia).

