#### Clinical parameters

2.7.1

The randomization visit (day 0) includes the collection of demographic variables [date of birth, sex, ethnicity], weight and height, clinical data [symptoms onset date, hospital admission date, clinical manifestations, radiological characteristics of pulmonary infiltrates], comorbidities [smoking and alcohol consumption, Charlson index], functional and cognitive assessment [Barthel and Pfeiffer index respectively], 8-point Ordinal scale (https://clinicaltrials.gov/ct2/show/NCT04280705), vital signs [temperature, blood pressure, heart rate, respiratory rate, oxygen assessment and supply (type of oxygen mask and FiO2, non-invasive or invasive ventilator support devices, or ECMO, PaO2/FiO2 and/or SatO2/FiO2), and conscious level using the Glasgow Coma Scale], as well as concomitant medication. With all these data we automatically calculate body mass index (BMI), the Pneumonia Severity Index (PSI) and CURB-65 index, and determine the extent of organ failure (SOFA score). The hospitalization visits include the collection of vital signs, 8-point Ordinal scale, adverse events and mortality. Visits on day +28 ± 3 and +56 ± 3 include vital signs, ordinal scale, relapse or worsening of the disease, adverse events and mortality.

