#### Primary end point

2.8.1

Average of days until *clinical stability* from treatment randomization.

Treatment failure is defined as: 1) patient who does not meet the criteria for clinical stability 56 days after starting treatment; 2) patient presenting with a grade 3 or 4 adverse event attributed to trial treatment; or 3) patient who dies after being included in the clinical trial.

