#### Statistical considerations

2.9.2

A descriptive analysis of the study variables will be carried out. Continuous variables will be described as mean and Standard Deviation (SD) or as median and range; and categorical variables as absolute frequencies and percentages. The main analysis will be performed when all patients reach clinical stability or failure. If patients are in hospital for 56 days, they will be considered clinical failures. Comparison between average time to achieve clinical stability between the two study groups will be measured using the log-rank test. To quantify the degree of association, hazard ratio will be estimated with a Cox proportional hazards model using a 95% confidence interval.

Efficacy analyses will be performed for the intention to-treat (ITT) population. If a proportion of subjects >10% is detected to have relevant deviations from the protocol (for example, non-compliance with the selection criteria, non-compliance or inability to receive the trial treatment), the per protocol (PP) analysis will exclude those subjects with such deviations. If this group is defined, all exploratory efficacy analyses will be repeated as a sensitivity test.

As additional analysis, a Cox proportional hazards model, adjusted for clinically relevant confounding factors such as age, sex, comorbidities using the Charlson index, indexes to assess the severity of pneumonia (PSI and CURB-65), index of organic dysfunction (SOFA) and inflammatory parameters will be performed. In addition, prespecified subgroup analyses involving sensitivity analysis will be used to evaluate outcomes in patients not receiving invasive mechanical ventilation.

For evaluation of secondary variables, we will calculate unadjusted and adjusted estimations of effect size and the corresponding 95% confidence intervals using linear, logistic or proportional hazards Cox regression. Study adverse events will be described according to their severity and relationship with other treatments, and will be compared between treatment groups. Midway through recruitment, i.e. 21 patients per arm, an intermediate efficacy and safety analysis will be performed. For this, a correction of the type I error will be applied following Lan-DeMets (O'Brien – Fleming) in evaluation of efficacy.

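### Clinical stability carries no condition on respiratory support, so a patient on low-FiO2 invasive ventilation or ECMO can be scored as a primary-endpoint event

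*Protocol article*

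**What the plan says.** Section 2.5 (Treatment) defines clinical stability as a state "which is achieved after fulfilling all of the following criteria for 48 consecutive hours: body temperature" at or below 37.5 °C, with "PaO2/FiO2 > 400 and/or SatO2/FiO2 > 300; and respiratory rate ≤24 rpm". The abstract gives the same list, and the Discussion names the same measures when it defends the endpoint as objective. No place requires the patient to be off, or weaned from, any form of support.

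Section 2.8.1 makes this the primary endpoint, in days "from treatment randomization". Its failure definition has three items: a "patient who does not meet the criteria for clinical stability 56 days after starting treatment", a grade 3 or 4 adverse event attributed to trial treatment, and death after inclusion. Section 2.9.2 adds: "If patients are in hospital for 56 days, they will be considered clinical failures".

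Invasive ventilation and ECMO appear elsewhere:
- Section 2.5, as a reason to stop study drug: "Experimental treatment is also discontinued if the included patient has a severe or potentially severe infection, required invasive mechanical ventilation", or ECMO.
- Section 2.7.1, as recorded data: "non-invasive or invasive ventilator support devices, or ECMO".
- Section 2.8.2, where the need for ventilatory support is a secondary endpoint.
- Section 2.9.2, where a subgroup or sensitivity analysis covers patients not invasively ventilated.

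Section 2.2.2 does not exclude ventilated patients at entry.

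**The concern.** In an intubated patient the respiratory rate can be set by the machine. Oxygenation is held by positive pressure or by the ECMO circuit. Dividing by FiO2 corrects for inspired oxygen but not for either of those. The numbers can therefore describe the support rather than the patient's recovery.

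The protocol treats the need for ventilation or ECMO as a reason to end experimental treatment, yet the same patient can be counted as having reached the trial's favourable outcome. Ventilated patients are expected in this population and stay in the intention-to-treat comparison. If intubation differs between arms, the scoring differs between arms too: early or false events would flatter the arm with more intubation. The trial is open-label, so the staff who set FiO2 and ventilator rate know the allocation.

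**Working it through.** **1. Can the criteria be met on support?** The and/or wording lets either ratio qualify.
- SatO2/FiO2 > 300 requires SatO2 > 300 × FiO2. At FiO2 0.30 that is SatO2 > 90%.
- Ventilated, SatO2 96%, FiO2 0.30, rate 18, 37.0 °C: 96/0.30 = 320. Qualifies.
- On ECMO, SatO2 93%, ventilator FiO2 0.30, rate 12, temperature within the limit: 93/0.30 = 310. Qualifies.
- Upper limit of this route: SatO2 cannot exceed 100%, so FiO2 must be below 100/300 = 0.333.
- The PaO2 route is harder: at FiO2 0.30 it needs PaO2 > 400 × 0.30 = 120. An assumed PaO2 of 80 gives 80/0.30 = 267 and fails, but the saturation route alone is enough.

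**2. Does another rule remove such a patient?**

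| Rule | Effect on the event |
|---|---|
| Stop study drug on ventilation or ECMO (2.5) | None. It is a treatment rule, and controls have no study drug to stop |
| Death is failure (2.8.1) | Names the patient a failure; silent on an earlier 48-hour event |
| 56 days in hospital is failure (2.9.2) | Same, and only for those in hospital that long |
| Analysis of patients not invasively ventilated (2.9.2) | Leaves the main analysis unchanged |

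**3. The planned sample size.** Freedman's formula with hazard ratio 0.52, two-sided 5% and 80% power gives 7.849 × (1.52/0.48)² = 78.7, so 79 events. 79/0.95 = 83.2, so 84 patients, or 42 per arm. The stated figure reproduces, and it counts every retained patient as an event.

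**4. Size, under assumptions only.** Inputs from section 2.9.1: about 40 evaluable per arm (42 × 0.95 = 39.9) and, for non-ventilated patients, medians of 16 and 16 × 0.52 = 8.3 days. Assumed, because the documents give none of these: the intubation shares; 50% of ventilated patients meeting the numbers for 48 hours on support, between days 8 and 25; 50% of ventilated patients ever truly stabilising, here 3 to 25 days after that point. In the override column, those who never truly stabilise are assumed to die or stay in hospital to day 56. The hazard ratio is experimental to control, so above 1 favours experimental.

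| Intubation, control/experimental | Support-free scoring | As written, failure overrides | As written, no override |
|---|---|---|---|
| 15% / 30%: hazard ratio | 1.12 | 1.16 | 1.33 |
| 15% / 30%: chance of significance | 8% | 10% | 24% |
| 30% / 15%: power | 74% | 71% | 69% |
| 20% / 20%: hazard ratio | 1.50 | 1.51 | 1.62 |

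In the first scenario the expected number meeting the numbers on support is (0.15 + 0.30) × 40 × 0.5 = 9 of 80. Two other simulations, differing in the timing of later recovery, gave 1.15 to 1.36 (significance 9% to 24%) and 1.09 to 1.32 (5% to 21%) without override. With a 20% share meeting the numbers on support, still without override, the shifts were 1.15 to 1.22 (9% to 14%) and 1.10 to 1.17 (6% to 11%).

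**The case against.** A reader might infer that nothing else in the protocol catches these patients. That goes too far. The death item in section 2.8.1 has no exemption for earlier stability, and section 2.9.2 makes 56 days in hospital a failure. The worst case, a patient scored stable who then dies on the ventilator, is named a failure. If those rules override an earlier event, what remains is mainly ventilated survivors discharged before day 56, most of whom would stabilise anyway and are only recorded some days early. This stands, with one limit: neither section says that a later failure cancels an earlier 48-hour event.

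A reader might also infer that the rule turns harm into apparent efficacy. The documents do not support that as a finding. They give no intubation rate and no share meeting the numbers on support. The route needs FiO2 below 0.333 on the saturation ratio for 48 consecutive hours without fever, and the effect nearly vanishes once the failure rules override.

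The planned non-ventilated analysis, ventilatory-support counts, ordinal scale and mortality would help expose a distortion. They do not correct the primary result.

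Finally, section 2.12.1 refers to a complete protocol that is not shown and might contain a support condition. But the article presents its list as all the criteria, so the definition as published gives a wrong event rather than merely leaving out a detail.

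**Conclusion.** The definition as stated admits patients on invasive ventilation or ECMO as primary events. That rests on the text and simple ratios, with no assumption about frequency.

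The consequence depends on precedence, which is not stated. If failure overrides, the remaining error is mainly early timing in ventilated survivors. If it does not, false successes remain as well. The size and direction of the bias are unknown. In the scenario with 15% intubation in control and 30% in experimental, the hazard ratio moves from about 1.1 to between about 1.16 (override) and 1.36 (no override), and by less if 20% rather than 50% meet the numbers on support. With the intubation shares reversed, the cost is a few points of power. These figures illustrate sensitivity and do not predict this trial's result. The sample-size calculation is not in error.

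**What to change.** For endpoint scoring only:
- Count clinical stability, in the primary endpoint and in the secondary endpoints on reaching and maintaining stability, only when the patient is without invasive mechanical ventilation and without ECMO throughout the 48 hours. Derive this from the support type recorded under section 2.7.1.
- State that failure by the criteria of sections 2.8.1 and 2.9.2 takes precedence over any 48-hour period met on such support.

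Section 2.5 uses the same definition to end experimental treatment. The sponsor should reconcile the two uses; no change to treatment is proposed here.

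The cost is one clause, one precedence statement and one derived variable. A few events come later or not at all, so event yield falls slightly. As illustration, 84 × 0.95 = 79.8 expected events. If 5% or 10% of retained patients ceased to be events, 75.8 or 71.8 would remain, and Freedman power would fall from 80.5% to 78.5% or 76.3%. Keeping 79 events would then take 88 patients (79/(0.95 × 0.95) = 87.5) or 93 (79/(0.95 × 0.90) = 92.4).

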### Study visits

2.6

All patients are followed from day 0 through day +56 or death. The planned visits are: 1) randomization visit (day 0) in which the patient is screened and eventually included in the study; 2) Hospitalization visits that are variable according to the period of admission; 3) Visits on day +28 ± 3 and on day +56 ± 3 from randomization. These visits are face-to-face to evaluate whether patients present a relapse or worsening of the disease, as well as the presence of adverse events or mortality. Specific procedures that are performed on each visit are detailed in Table 1 and the *evaluation methods* section.

**Table 1 tbl1:** Flow-chart of the trial showing the procedures that will be conducted in each visit.

	Randomization visit (day 0)	Hospitalization visits (days n)	Visit 28 ± 3 days after the start of treatment	Visit 56 ± 3 days after the start of treatment
Inclusion/exclusion	x			
Informed consent	x			
Randomization	x			
Demographics Comorbidities	x			
COVID-19 clinical data	x			
Vital signs	x	x	x	x
8-point Ordinal scale	x	x	x	x
Analysis (Hematology, Chemistry, Coagulation)	x	x	x	x
Tacrolimus levels		x		
Cytokines	x	x	x	x
Viral load (blood)	x	x	x	x
Nasopharyngeal SARS-CoV-2 PCR	x		x	x
Clinical stability	x	x	x	x
Lung tests (x-ray, CT scan, chest US, 6MWT, functional tests)	x	x (1)	x (1)	x
Study treatment	x	x	x	x
Concomitant medication	x	x	x	x
AE registration	x	x	x	x

(1) according to the attending physician.

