#### Determination of sample size

2.9.1

The median time to clinical stability in the control group is expected to be 16 days. If the hazard ratio of clinical stability of control patients in relation to the patients in the experimental group were 0.52, it would be necessary to include 42 patients in each group in order to be able to reject the null equality hypothesis with a power of 80%. The probability of Type I error associated with this hypothesis test is 0.05 and includes 5% of withdrawal.

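### Read literally, the stability rule lets SatO2/FiO2 above 300 suffice with no minimum saturation, so a patient enrolled with PaO2/FiO2 below 300 on low-flow oxygen can reach the primary endpoint without improving

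*Protocol article*

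**What the plan says.** - **Entry** (Protocol article, 2.2.1 Inclusion criteria): "Respiratory failure (PaO2/FiO2 <300 or satO2/FiO2 <220"). Either ratio is enough. The other criteria are a positive PCR, new infiltrates and raised inflammatory markers. Fever and a raised respiratory rate are not required.
- **Who is enrolled** (2.2 Population): patients enter "if they meet all the inclusion criteria and there is no reason for exclusion". Nothing in 2.2.2 Exclusion criteria removes a patient who is already within the stability limits.
- **Stability** (2.5 Treatment): temperature ≤37.5 °C, together with "PaO2/FiO2 > 400 and/or SatO2/FiO2 > 300; and respiratory rate ≤24 rpm", all held for 48 consecutive hours. The abstract has the same rule: "PaO2/FiO2 > 400 and/or SatO2/FiO2 > 300, and respiratory rate ≤24 rpm; for 48 consecutive hours". Neither place gives a minimum saturation, a room-air condition or a required change from baseline.
- **Use of the rule**: time from randomization to stability is the primary endpoint (2.8.1), and stability ends the trial drug (2.5: "The experimental treatment is discontinued after" it).
- **Day 0 data**: 2.7.1 Clinical parameters collects "oxygen assessment and supply (type of oxygen mask and FiO2, non-invasive or invasive ventilator support devices, or ECMO, PaO2/FiO2 and/or SatO2/FiO2"). Table 1 ("Flow-chart of the trial showing the procedures that will be conducted in each visit") marks clinical stability at the day 0 visit.
- **Design assumption** (2.9.1): "The median time to clinical stability in the control group is expected to be 16 days".

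**The concern.** The two PaO2/FiO2 limits leave a gap between below 300 (entry) and above 400 (stability), and so do the two SatO2/FiO2 limits, below 220 and above 300. The gap disappears when a patient enters on one ratio and is judged stable on the other. Because SatO2/FiO2 carries no saturation floor, it is very easy to satisfy at low FiO2.

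A patient who is in respiratory failure by the entry rule could then be counted as a primary-endpoint success about two days after randomization, with no change in oxygenation. Early events of this kind, if equally frequent in both arms, say nothing about treatment and weaken the comparison. In the experimental arm the same rule would also stop tacrolimus after about 48 hours.

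**Working it through.** **1. The plan's own figure.** Inputs from 2.9.1: hazard ratio 0.52, power 80%, type I error 0.05 (taken as two-sided), 5% withdrawal. Freedman's formula gives (1.52/0.48)² × (1.96 + 0.84)² ≈ 79 events, and 79/0.95 = 83.2, rounded up to 84, or 42 per arm. The sample size reproduces and is not in question.

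**2. Saturation needed for SatO2/FiO2 > 300.** The formula is SatO2 > 300 × FiO2.

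| FiO2 | SatO2 needed |
|---|---|
| 0.21 | > 63% |
| 0.24 | > 72% |
| 0.28 | > 84% |
| 0.30 | > 90% |
| 0.32 | > 96% |
| 1/3 or more | cannot be met (100/(1/3) = 300, not above it) |

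**3. One gas, both rules.**
- FiO2 0.28, PaO2 70 mmHg, SatO2 94%: 70/0.28 = 250 (eligible); 94/0.28 = 336 (within the oxygen limit).
- Room air, PaO2 60 mmHg, SatO2 91%: 60/0.21 = 286 (eligible); 91/0.21 = 433 (within the oxygen limit).

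**4. Width of the overlap.** Pairing PaO2 with SatO2 needs a dissociation curve, which the document does not give. The Severinghaus curve is assumed here. The lower end is the PaO2 at which SatO2 equals 300 × FiO2, divided by FiO2. The upper end is the entry limit of 300.

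| FiO2 | PaO2 at the lower end (mmHg) | PaO2/FiO2 range meeting both rules | SatO2/FiO2 when PaO2/FiO2 = 300 |
|---|---|---|---|
| 0.21 | 32.7 | 156–300 | 437 |
| 0.24 | 37.9 | 158–300 | 393 |
| 0.28 | 48.7 | 174–300 | 344 |
| 0.30 | 58.7 | 196–300 | 323 |
| 0.32 | 81.9 | 256–300 | 305 |

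At PaO2/FiO2 = 300 the SatO2 ratio falls to 300 at FiO2 0.325, so the overlap ends there. Shifting the curve by ±3 mmHg in P50 moves the lower ends to 138–173 at 0.21, 154–193 at 0.28 and 227–285 at 0.32. The overlap remains.

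**5. Possible effect on power.** Assumptions: 40 evaluable patients per arm (42 less 5%), exponential times, control median 16 days, hazard ratio 1/0.52 = 1.92 in favour of the experimental arm, 56 days of follow-up, two-sided 0.05 log-rank test, no interim look. A given share of patients in both arms reaches stability on day 2. The share is an assumption; the document gives none.

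| Share | Power, all patients | Power, overlap patients left out |
|---|---|---|
| 0% | 80.7% | 80.5% |
| 5% | 76.7% | 78.6% |
| 10% | 72.4% | 76.0% |
| 20% | 63.6% | 71.1% |

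Repeat simulations agree within simulation error (73% and 74% at a 10% share), hence the rounded figure of about 73%. If 16 days is instead the median of all controls, overlap patients included, the full-analysis figures at 5%, 10% and 20% are 75.8%, 71.9% and 60.4%.

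**The case against.** **The wording has a second reading.** Section 2.7.1 uses *and/or* for whichever ratio was recorded. Carried over to the stability rule, both ratios must pass when both are known, and either serves when only one is. Both worked examples would then fail stability, and the gap would remain only where no gas is repeated during the 48 hours. This stands: the text supports either reading. A reader might infer that the plan deliberately lets saturation override a failing blood gas, and the document does not say so. The rule is nevertheless stated in two places without settling the matter, and it defines the primary endpoint.

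**The consequence is conditional.** A reader might infer that some patients are stable on day 0. They cannot be, because 48 hours are required. Counting as stable at about day 2 needs low FiO2, temperature ≤37.5 °C and respiratory rate ≤24, all sustained, in a population selected for severe, hyperinflammatory disease. The expected control median of 16 days suggests that few such patients were foreseen. This stands too.

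**Power need not fall.** If treatment prevents early worsening, overlap patients do carry contrast. In one illustrative scenario, 60% of control and 30% of experimental overlap patients fail to hold the limits. Power then stays at about 81% at shares of 10% and 20%, while leaving these patients out lowers it to about 75% and 70%. So the loss in the working depends on equal timing in both arms, and the exclusion analysis belongs beside the primary analysis, not in its place.

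**Unblinded staff set the FiO2.** A reader might infer biased stability dates. The document gives nothing from which to judge the size or direction of that effect, and the Discussion claims only to minimize the impact of the open design. It is not part of this point.

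**Conclusion.** The point holds in limited form. Under the literal reading, a patient enrolled through PaO2/FiO2 below 300 on FiO2 below about 0.325 can be within the oxygen limit of stability from day 0. If the other two limits also hold for 48 hours, that patient counts as reaching the primary endpoint without improving. On room air this hardly depends on the assumed curve, since any saturation above 63% passes. Patients who enter through SatO2/FiO2 below 220, or who are on FiO2 of 1/3 or more, are not affected at entry.

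The number affected is unknown and probably small. With equal timing in both arms the effect is dilution, illustratively from 80% to about 73% power at a 10% share. It would be wrong to read this as a route to false benefit, because events shared equally by both arms do not create a difference. The flaw lies in how two fully stated rules interact, so it is not a detail that the article merely left out. It is worth settling before analysis because doing so is cheap.

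**What to change.** 1. **Settle the wording.** State that when both ratios are recorded in the 48-hour window, a PaO2/FiO2 below 300 is not overridden by a SatO2/FiO2 above 300. If the primary definition is to stay as it is, apply this in a prespecified sensitivity derivation of the stability date. Show that derivation with and without the blood-gas check, because gases are taken at the discretion of unblinded staff and the check works only where one was taken.
2. **Prespecify a repeat of the log-rank and Cox analyses** without patients who meet all three stability limits on day 0, using values taken before the first dose, and report their number by arm. The group is defined before treatment, so the randomized comparison is preserved.

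A saturation floor alone would not do the work of item 1. On the assumed curve, 92% corresponds to PaO2 63.8 mmHg, which is PaO2/FiO2 304 on room air but 266 at FiO2 0.24 and 228 at 0.28.

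**Cost.** A few lines of analysis-plan text and one extra derivation from data already collected. The repeat analysis uses somewhat fewer patients: at a 10% share, about 36 of 40 evaluable per arm. Eligibility and sample size are unchanged. Anything added after the interim analysis at 21 patients per arm must be labelled as such. If only the sensitivity derivation is adopted, the early stop of tacrolimus in such patients remains and should be acknowledged.
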